### Adverse Events

All adverse events in the 12-month study period were recorded by following the Good Clinical Practice and Health Research Authority processes. Nonserious adverse events such as constipation, fatigue, or hair loss were recorded when participants informed the trial team.

### Qualitative Evaluation

In-depth semistructured interviews were conducted with a subset of 10 ILED and 10 CLED participants at the end of the active weight loss phase (ILED week 28, CLED week 12). HCPs (n=6) delivering the programs were also interviewed near study completion. All interviews were conducted by an independent research assistant trained in qualitative interview techniques. Interviews explored the participant and HCP experiences of the ILED and CLED programs and the use of the Oviva app. Purposive sampling was used to select trial participants with a range of success in terms of actual weight loss and HbA_1c_ reduction, as well as participants' perceived success. Participants with ethnicities other than White-British were included where possible, with a fairly even split between men and women. All participants gave written informed consent to be interviewed and were assured that their data would be anonymized. The interviews were audiorecorded and transcribed verbatim for thematic analysis.

### Sample Size and Statistical Analysis

The total number of participants recruited for the study was 79. The sample size was selected to allow an estimate of uptake within ±6.6% of the target uptake of 10% [55] with 95% confidence while allowing the research team to obtain sufficient data on the feasibility and potential efficacy of the ILED and CLED.

This study will not undertake significance tests of changes to the primary outcome measures. Descriptive, graphical (summary), and basic inferential statistics of outcomes will be presented as appropriate, for example, frequencies and percentages, mean and SD, or median and quartiles. Confidence intervals (95%) will be calculated to show the change from baseline in the outcomes for each group.

Questionnaires used as outcome measures are quantitative and will be analyzed using appropriate descriptive statistics as per standard.

Changes to diabetes medication will be presented using the medication effect score (MES). The MES for a participant is the sum of the MES for each of their individual medications, where MES=actual drug dose/maximum drug dose×drug mean adjustment factor. A decrease in MES corresponds to a decrease in the use of diabetes medications [56]. Changes to BP medications will be presented using a Treatment Intensity Score (TIS) defined as the actual drug dose/maximum drug dose [57]. The TIS for a participant is the sum of the TIS for each of their medications, and a decrease in TIS indicates a decrease in BP medications.

An ITT analysis using multiple imputations will conducted for percentage weight loss, HbA_1c_, and MES. All other outcomes will be presented only for those who completed the trial.

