### Recruitment

Potential eligible participants were recruited from 3 settings using the following methods:

Patients in three general practices in Manchester were sent targeted invite letters and a text message reminder 8 weeks later if there was no response. These practices included a population of patients with T2D ranging from 400 to 700 and reflected different levels of deprivation in England. The England Index of Multiple Deprivation (IMD) score for each practice was 10.9 (least deprived 25% in England) and 29.8 and 44.1 (top 25% deprived in England) [36].Patients at MFT and Stockport NHS Foundation Trust were invited to the study via patient record search and invitation letter, using poster displays, or during face-to-face routine clinical contacts.Patients with T2D (n=2500) on the Help BEAT Diabetes volunteer database (hosted by the National Institute of Health Research Clinical Research Network for Greater Manchester) were contacted via mail or email and asked to check if they met the eligibility criteria for the trial and to contact the MIDDAS trial team if they were interested in taking part.

Those invited by letter had the opportunity to tell the trial team why they did not wish to take part via an anonymous reply slip. Interested patients were invited to an optional group session at MFT to receive more information on the diets and try the Optifast meal replacements before deciding to participate.

The inclusion and exclusion criteria for the trial is detailed in Textbox 1.

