### Outcomes

#### Primary

Uptake: To achieve an uptake of at least 10% from a primary care mail out.The proportion of subjects in the ILED and CLED groups who successfully lost and maintained >15% weight loss at 12 months, as determined by intention-to-treat (ITT) analysis.The proportion of subjects in both groups who achieved HbA_1c_ <48 mmol per mol (6.5%) at 12 months using ITT analysis.Retention: Aiming for a retention of 60% (48/79) completion as measured by attendance at the 12-month appointment. This is the acceptable completion rate in NICE guidance for commissioning weight management services in England [48].

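### The ±6.6% precision given for uptake takes about 79 to 80 people as its denominator, but uptake is measured on patients mailed, so it does not justify recruiting 79

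*Protocol article*

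**What the plan says.** Sample Size and Statistical Analysis opens with the size of the trial, "The total number of participants recruited for the study was 79", and then gives the reason: "The sample size was selected to allow an estimate of uptake within ±6.6% of the target uptake of 10% [55] with 95% confidence". The same sentence adds a second reason without a number, namely that the trial should yield enough information on feasibility and possible efficacy.

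Under Outcomes, Primary, the uptake target is worded as "To achieve an uptake of at least 10% from a primary care mail out". The Recruitment section describes that mail-out: letters to selected patients in three Manchester general practices, followed by a text reminder. On practice size it says "These practices included a population of patients with T2D ranging from 400 to 700". Recruitment and the Abstract also name two other sources of participants: two hospital trusts and a volunteer research register. The article does not say how many patients were mailed.

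**The concern.** Uptake is a fraction of the people invited. The people recruited are those who said yes, so they belong in the numerator. A sample-size statement that uses the number recruited as the binomial denominator describes the precision of some other proportion. Here the number recruited is not the right numerator either, because some of the 79 did not come through the mail-out.

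This is the only quantitative support for the trial size. The Goals section makes uptake one of the estimates that will decide whether a full trial is indicated. A margin that does not belong to uptake could lead a reader to judge the result against the wrong yardstick. For example, an observed uptake of 6% lies within 6.6 points of the 10% target, but outside the ±2.1 points that 790 independent invitees would give.

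**Working it through.** **Inputs from the article.** Target uptake p = 0.10, half-width 6.6 points, 95% confidence and 79 recruited (Sample Size and Statistical Analysis); uptake defined on the primary care mail-out (Outcomes, Primary); three practices with 400 to 700 patients with type 2 diabetes, read as per practice (Recruitment).

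**1. Reproducing the printed figure.** The two-sided normal-approximation half-width is 1.96 × √(p(1 − p)/n).

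- n = 79: 1.96 × √(0.09/79) = 6.62 points.
- n = 80: 1.96 × √(0.09/80) = 6.57 points.
- Solved for n: 1.96² × 0.09/0.066² = 79.4. Any half-width that rounds to 6.6 needs n between about 78.2 and 80.6.

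Other constructions do not fit at this size. The Wilson half-width is 6.72 (n = 79) or 6.68 (n = 80). With a continuity correction it is 7.25 or 7.20. A one-sided 95% bound would need n of about 56. The arm sizes of 39 and 40 give 9.4 and 9.3.

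**2. Can that n be the number mailed?** With 79 mailed, 10% uptake gives 0.10 × 79 = 7.9, about 8 recruits. That is not a mailing meant to supply a trial of this size.

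**3. Is the margin a relative one?** ±6.6% of 10% is ±0.66 points, which needs 1.96² × 0.09/0.0066² ≈ 7,900 invitees. Three practices hold at most 3 × 700 = 2,100 patients with type 2 diabetes, so this reading fails.

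**4. Half-width on the mailed denominator.** The number mailed is not given, so these are illustrations at 10% uptake with invitees treated as independent:

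| Number mailed | Where the number comes from | Half-width (points) |
|---|---|---|
| 300 | assumed, no source in the article | ±3.4 |
| 790 | would yield 79 recruits at 10% if all came by mail | ±2.1 |
| 1,200 | 3 × 400, every patient mailed | ±1.7 |
| 2,100 | 3 × 700, every patient mailed | ±1.3 |

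The last two rows are upper bounds on the number mailed, because the letters were targeted and eligibility was restricted. On the independence assumption, any mailing above about 80 patients gives a margin narrower than ±6.6.

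**5. Clustering.** The invitees come from three practices that differ widely in deprivation. Assume an intraclass correlation of 0.01 and 790 invitees split equally, about 263 per practice. The design effect is 1 + 262 × 0.01 ≈ 3.6, and ±2.1 becomes 2.09 × √3.62 ≈ ±4.0. To reach ±6.6 at 790 mailed, the design effect would have to be (6.6/2.09)² ≈ 10, an intraclass correlation of about (10 − 1)/262 ≈ 0.034. The article gives no value for this correlation.

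**6. A proportion that 79 does determine.** For 60% retention, 1.96 × √(0.6 × 0.4/79) = 10.8 points.

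**The case against.** The strongest reply is that the slip does little harm. On the illustrative figures the printed margin is wider than the real one, so nobody is led to think uptake is known more precisely than it is. No decision rule uses ±6.6%, no significance tests of the primary outcomes are planned, the Discussion says the trial was not powered to compare the groups, and recruitment is complete. The same sentence also gives a second reason for the size, which this error does not touch. All of this stands. It makes the point moderate but does not make the figure right.

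Four stronger readings are tempting, and the documents do not support them.

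- *That the 79 recruits were certainly the input.* The denominator is never named, and 80 fits equally well. The retention target, printed as 60% (48/79), suggests a planned 80: 48/80 = 60.0%, while 48/79 = 60.8%. Either number is a count of participants, so the fault is the same.
- *That the margin is 2 to 5 times too wide.* That ratio depends on an unstated number mailed, on the whole practice population being mailed at its upper end, and on independence.
- *That hospital and register recruits will be counted in uptake.* The outcome is already limited to the mail-out. Only the justification sentence is at fault.
- *That the article should have given precision for retention, weight loss and HbA1c.* A condensed article may leave this to the full protocol or the analysis plan, so its absence is no finding.

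**Conclusion.** The concern holds as an error in one stated figure. ±6.6% is the half-width for a 10% proportion measured in about 79 to 80 people, and uptake is not measured in that group. Nothing in the article supplies a mailed denominator of that size. The only numerical justification for recruiting 79 therefore fails as written.

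The printed margin is probably too wide for uptake: about ±1.3 to ±3.4 points would apply for 2,100 down to 300 mailed. This rests on assumed mailing numbers, on reading 400 to 700 as per practice, and on independent invitees. Clustering by practice would widen the range and, if strong enough, could close the gap. The error is conservative for uptake, so it should not be read as showing that uptake is poorly estimated. It is a moderate correction and does not threaten the trial's conclusions.

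**What to change.** Withdraw the ±6.6% statement as the basis for 79. State the number of patients mailed in the three practices and give the uptake precision on that number. In the results, report the uptake confidence interval with patients mailed as the denominator and mail-out recruits as the numerator, and say whether clustering by practice was allowed for. If a numerical rationale for 79 is kept, base it on a proportion measured in randomised participants, for example 60% retention, ±10.8 points at n = 79.

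The cost is one reworded paragraph, a short recalculation and a count of letters sent. Enrolment does not change.

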**Methods:**

A total of 79 participants were recruited from primary care, two National Health Service hospital trusts, and a voluntary T2D research register in the United Kingdom. The participants were randomized to a remotely delivered ILED (n=39) or CLED (n=40). The active weight loss phase of CLED involved 8 weeks of Optifast 820 kcal/3430 kJ formula diet, followed by 4 weeks of food reintroduction. The active weight loss phase of ILED (n=39) comprised 2 days of Optifast 820 kcal/3430 kJ diet and 5 days of a portion-controlled Mediterranean diet for 28 weeks. Both groups were asked to complete 56 Optifast 820 kcal/3430 kJ days during their active weight loss phase with an equivalent energy deficit. The diets were isocaloric for the remainder of the 12 months. CLED participants were asked to follow a portion-controlled Mediterranean diet 7 days per week. ILED followed 1-2 days per week of a food-based 820 kcal/3430 kJ diet and a portion-controlled Mediterranean diet for 5-6 days per week. Participants received high-frequency (weekly, fortnightly, or monthly depending on the stage of the trial) multidisciplinary remote support from a dietitian, nurse, exercise specialist, and psychologist via telephone or the Oviva smartphone app. The primary outcomes of the study were uptake, weight loss, and changes in glycated hemoglobin at 12 months. An outcome assessment of trial retention was retrospectively added. Secondary outcomes included an assessment of adherence and adverse events. A qualitative evaluation was undertaken via interviews with participants and health care professionals who delivered the intervention.

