#### Secondary

##### Process Measures

Participant adherence to the protocol including self-reported adherence to LED days, preference for face-to-face contact with the dietitian, preference for food-based LED days over Optifast, and attendance at follow-up appointments.Download and usage of the Oviva app for self-monitoring.

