##### Exploratory Measures

Change in the following measures across the 12-month study period:

Body fat and fat-free mass (bioelectrical impedance)Waist and hip circumferenceBP, lipid profile, and fasting blood glucose levelsNumber and dosage of diabetes and BP medicationsSelf-efficacy for eating, anxiety, depression, and quality of life (as measured by WEL-SF [38], GAD-7 [39], PHQ-9 [40] and Audit of Diabetes-Dependent Quality of Life (ADDQoL) [49] questionnaires, respectively)Quality of diet on non-LED days (as measured by the Mediterranean diet score questionnaire [50])PA (as measured by the Scottish Physical Activity Questionnaire [51])Self-reported satisfaction with weight loss was measured using a 7-point Likert scale. This is highly relevant for the comparison of ILED and CLED, where the CLED will experience faster initial weight loss and achievement of their weight loss goal than the ILED arm [52]Serious adverse events reported up to the end of the 12-month trial

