### Retention and Withdrawal

Participants had the right to withdraw from the trial at any time. Participants were considered as withdrawn from the trial if they withdrew from the study intervention voluntarily or if they failed to return for follow-up assessments. Participants could also be removed by the principal investigator if this was considered necessary for medical reasons or due to ineligibility arising during the study (eg, pregnancy). Reasons for withdrawal were recorded, and their GP was notified with recommendations for follow-up care where appropriate. Participants who withdrew continued to have weight and HbA_1c_ collected from their routine diabetes clinic or GP visits for the duration of the 12-month trial unless they did not consent to this at baseline. No incentives were provided to the participants to promote retention and follow-up.

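### As written, the completers-only rule covers serious adverse events, diet adherence, attendance and app use, so withdrawn participants drop out of the safety and feasibility results

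*Protocol article*

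**What the plan says.** Under Sample Size and Statistical Analysis, the article sets two analysis sets. The first is for three outcomes: "An ITT analysis using multiple imputations will conducted for percentage weight loss", with HbA1c and the medication effect score named in the same sentence. The second is for everything else: "All other outcomes will be presented only for those who completed the trial".

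The Outcomes section shows what everything else contains:

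- Under Process Measures: "Participant adherence to the protocol including self-reported adherence to LED days", together with preference for face-to-face dietitian contact, preference for food-based LED days and attendance at follow-up. The next item is "Download and usage of the Oviva app for self-monitoring".
- Under Exploratory Measures: "Serious adverse events reported up to the end of the 12-month trial", alongside body composition, blood pressure, lipids and questionnaires.

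The Abstract (Methods) agrees that these are outcomes: "Secondary outcomes included an assessment of adherence and adverse events".

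Under Primary outcomes, completion is measured by attendance at the 12-month appointment, with a target of 60% (48/79). Under Retention and Withdrawal, participants count as withdrawn if they stop the intervention or do not return, and "Participants could also be removed by the principal investigator if this was considered necessary for medical reasons". The Adverse Events section says "All adverse events in the 12-month study period were recorded".

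**The concern.** Restricting a measurement to completers is defensible when it can only be taken at the final visit. Safety and process outcomes are different: they accrue from randomisation onwards, and leaving the programme is part of what they should describe. A participant removed on medical grounds would not appear in a completers-only table of serious adverse events. Someone who abandoned the LED days in week 3 would not appear in the adherence summary.

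The primary aim is feasibility (Goals of This Study), and the Discussion says the trial will add to limited safety data on insulin-treated patients following these diets. The pilot plans no significance tests of its primary outcomes, so descriptive figures are its main product and their denominator decides what they mean. They are also meant to inform the case for a definitive trial.

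**Working it through.** **1. The plan's own retention figure.** 48/79 = 60.8%, and 47/79 = 59.5%. So 48 is the smallest whole number that reaches 60% of 79, and the stated target reproduces.

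**2. How many the rule leaves out.** Number excluded = randomised minus completers, taking completion as attendance at 12 months, as in the retention outcome.

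- At the retention target: 79 − 48 = 31, and 31/79 = 39%.
- At the roughly 25% attrition that the Introduction cites for intensive continuous low-energy-diet studies: 0.25 × 79 = 19.75, about 20 of 79.

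**3. Does any passage exempt these outcomes?** The Adverse Events section covers recording. The Trial Steering Committee and Trial Management Group section covers evaluation and oversight. Remote Behavioral Support says requests for face-to-face consultations were recorded in both arms. None of these sets an analysis set, so none overrides the sentence in the analysis section.

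**4. What the rule does to each outcome.**

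- *Adverse events:* events in withdrawn or medically removed participants are recorded but not presented.
- *Attendance:* week-52 attendance is already covered by the primary retention outcome over 79. Attendance at weeks 8, 12 and 28 would be described only in people already known to have attended at 12 months.
- *LED-day adherence:* the arms complete their 56 formula days on different timetables. The continuous arm does 8 weeks × 7 days = 56. The intermittent arm does 28 weeks × 2 days = 56. A participant lost at week 20 could have done all 56 in the continuous arm, but at most 20 × 2 = 40 in the intermittent arm. Dropping non-completers therefore discards different adherence information in each arm.

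**5. How far the figures could move.** The documents give no event or adherence rates. The rates below are assumed, to show the range only.

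Serious adverse events: assume 5% risk in completers and k × 5% in non-completers, with k from 1 to 4. The completer table shows 5% throughout.

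| Non-completers | All-randomised risk, k = 1 | All-randomised risk, k = 4 | Share of affected participants left out |
|---|---|---|---|
| 31 of 79 | 5.0% | (2.40 + 6.20)/79 = 10.9% | 39% to 72% |
| 20 of 79 | 5.0% | (2.95 + 4.00)/79 = 8.8% | 25% to 58% |

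Adherence: assume completers do 90% of LED days and non-completers 30% to 70%.

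- With 31 non-completers: (0.9 × 48 + 0.3 × 31)/79 = 66%, up to (0.9 × 48 + 0.7 × 31)/79 = 82%.
- With 20 non-completers: (0.9 × 59 + 0.3 × 20)/79 = 75%, up to (0.9 × 59 + 0.7 × 20)/79 = 85%.

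The completer summary would read 90% in every case. At k = 1 the serious adverse event rate is unbiased, but 39% or 25% of the affected participants are still missing from the table.

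**The case against.** The strongest reply is that the sentence was not meant this way. Read literally it would also cover uptake and retention, which cannot be restricted to completers: uptake is measured on people mailed, and retention is set against 79. The sentence directly follows the one on multiple imputation, in a section on change from baseline. It was probably written with clinical and questionnaire measures in mind. The safety outcome runs to the end of the 12-month trial, all events were recorded and evaluated, and the full protocol or a separate analysis plan may define a safety set.

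Much of this stands. A reader might infer that the team decided to withhold events in people who dropped out; the documents do not show that. But the wording is an affirmative rule without exception, and the passages on recording and oversight do not change it. If a narrower scope was intended, the sentence should say so.

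Four further limits also stand:

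- After withdrawal, only weight and HbA1c are named as still collected. LED-day adherence was reported at dietitian contacts, so it may end when contact ends. App use was optional, and the article does not say how usage was captured. It cannot be assumed that complete data exist for all 79.
- Week-52 attendance is not lost, because it is the retention outcome.
- The trial is not powered for differences between arms, so the unequal loss of adherence information matters for description rather than for a formal comparison.
- For exploratory measures in a descriptive pilot, openly labelled completer summaries are a legitimate choice. A repeated-measures model would be a preference, not the correction of an error.

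**Conclusion.** The point holds for safety and process outcomes. As written, the rule leaves non-completers out of the results for serious adverse events, LED-day adherence, contact and food-based preferences, attendance and app use: 31 of 79 (39%) at the retention target, or about 20 of 79 at the cited attrition. Both counts assume that completing means attending at 12 months; actual retention is not in the document.

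A reader might go further and conclude that the rule understates harm and overstates adherence by a known amount. The documents do not support that. That non-completers had more events or poorer adherence is a plausible inference, helped by the provision for medical removals, but it is not stated, and the ranges above rest on assumed rates. What can be said is that completers-only figures answer a different question from the one a feasibility trial asks.

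**What to change.** Amend the sentence in Sample Size and Statistical Analysis so that:

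- Adverse events (serious, and nonserious as recorded), LED-day adherence, app use and attendance at each visit are reported by arm for all randomised participants, using data observed up to withdrawal or last contact.
- Follow-up time and the number with missing adherence data are given beside these results. LED days not observed are shown as such, not silently counted as done or not done.
- Completers-only presentation is limited to measures that need the 12-month visit (body composition, blood pressure, lipids, questionnaires) and is labelled as completers-only.

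The cost is a rewritten sentence and modest programming. No new data collection is needed, because the request stops at what was observed. The downside is that adherence may be incomplete after withdrawal and may look less favourable than in completers.

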### Continuous and Intermittent Low-Energy Diets

Intensive face-to-face weight loss programs using continuous low-energy diets (CLEDs) that provide approximately 800 kcal (3347 kJ) per day of formula-based total diet replacement for 8 to 20 weeks or longer are highly effective for large weight loss and remission from T2D [11-14]. The recently published Diabetes Remission Clinical Trial (DiRECT) tested an intensive CLED program in primary care and found that it was superior to standard best practice care (standard daily moderate energy restriction advice with minimal support). At 12 months, 45.6% (68/149) participants of the intervention group achieved remission with an average weight loss of 10 kg compared with 4.0% (6/149) and 1 kg loss in the control group (*P*<.001). Remission was highest (31/36, 86%) in those who achieved 15% weight loss [13] and is more likely in those diagnosed with T2D in more recent years [15].

The CLED approach using total diet replacement is thought to be effective because the initial rapid weight loss can be highly motivating [16], and formula diets remove decision making around food choices. In addition, subjective hunger may be reduced by the associated ketosis [17]. CLEDs have been shown to reduce excess fat in the liver and pancreas in patients with T2D, which is part of the proposed mechanism for T2D remission [11,18].

Possible drawbacks of the CLED approach are that it is not appealing to or achievable for everyone. Participants following CLED programs report shame and awkwardness in social situations centered around food [19]. Attrition in intensive CLED studies on people with overweight or obesity (+/−T2D) is approximately 25% [13,20], although higher rates have been reported in studies with less frequent health care professional (HCP) contact [14]. The prevention of weight gain following a CLED program remains a key challenge. In 2 years, participants in the CLED group in the DiRECT trial appeared to have regained approximately 40% of the weight they had lost after the initial total diet replacement phase despite regular face-to-face support and an intensive 2-year relapse program involving repeated spells of a CLED, partial meal replacements, and antiobesity medications [13,21].

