**Assessments**						
	Height	✓	—	—	—	—
	Weight	✓	✓	✓	✓	✓
	Waist circumference	✓	✓	✓	✓	✓
	Hip circumference	✓	✓	✓	✓	✓
	Body fat or fat-free mass (impedance)	✓	✓	✓	✓	✓
	Blood Pressure, heart rate^c^	✓	✓	✓	✓	✓
	Blood lipids, liver function, renal profile	✓	—	—	✓	✓
	Fasting plasma glucose	✓	✓	✓	✓	✓
	Laboratory HbA_1c_^d^	✓	—	✓	✓	✓
	Pregnancy urine test	✓	✓	✓	✓	✓
	BES^e^ questionnaire	✓	—	—	✓	✓
	AUDIT^f^ questionnaire	✓	—	—	✓	✓
	WEL-SF^g^ questionnaire	✓	—	—	✓	✓
	PHQ-9^h^ questionnaire	✓	✓	✓	✓	✓
	GAD-7^i^ questionnaire	✓	✓	✓	✓	✓
	EQ-5D-3L^j^ questionnaire	✓	—	—	✓	✓
	ADDQoL^k^ questionnaire	✓	—	—	✓	✓
	Mediterranean diet score	✓	—	✓	✓	✓
	S-PAQ^l^, PAR-Q^m^	✓	—	✓	✓	✓
	Self-satisfaction with the weight loss question^n^	—	✓	✓	✓	✓
	Participant qualitative interviews	—	—	✓ (CLED^o^)	✓ (ILED^p^)	—
	Health care professional qualitative interviews	—	—	—	—	✓

^a^Event or assessment occurred at this time point.

^b^Event or assessment did not occur at this time point.

^c^Further investigation with an ECG if heart rate <50 beats per minute and not on beta-blockers.

^d^HbA_1c_: glycated hemoglobin.

^e^BES: Binge Eating Scale.

^f^AUDIT: Alcohol Use Disorders Identification Test.

^g^WEL-SF: Weight Efficacy Lifestyle Questionnaire Short Form.

^h^PHQ-9: Patient Health Questionnaire scale-9.

^i^GAD-7: Generalized Anxiety Disorder scale-7.

^j^EQ-5D-3L: Measure of health-related quality of life.

^k^ADDQoL: Audit of Diabetes-Dependent Quality of Life.

^l^S-PAQ: Scottish Physical Activity Questionnaire.

^m^PAR-Q: Physical Activity Readiness Questionnaire.

^n^Given the effort you put into following the diet and exercise plan, how satisfied are you with the amount of weight you have lost or gained during the past month? 1=very dissatisfied to 7=very satisfied.

^o^CLED: continuous low-energy diet.

^p^ILED: intermittent low-energy diet.

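### The completer-only rule drops PHQ-9 and GAD-7 scores already collected from participants who miss the 12-month visit, and could make a diet look better tolerated than it was

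*Protocol article*

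**What the plan says.** Sample Size and Statistical Analysis reserves intention-to-treat analysis with multiple imputation for three outcomes: percentage weight loss, HbA1c and the medication effect score. It then states: "All other outcomes will be presented only for those who completed the trial".

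Exploratory Measures lists 12-month change in anxiety (GAD-7) and depression (PHQ-9), so both come under that rule. Table 1 schedules both at baseline and at weeks 8, 12, 28 and 52.

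The analysis section does not define completing the trial. The only measure in the article is in the primary outcome on retention: "completion as measured by attendance at the 12-month appointment", with a target of 48/79.

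For people who leave, Retention and Withdrawal says: "Participants who withdrew continued to have weight and HbA_1c_ collected from their routine diabetes clinic or GP visits", subject to consent given at baseline. It names no questionnaire.

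**The concern.** Scores from weeks 8, 12 and 28 are available for many people who do not reach week 52. They need no imputation to be shown, yet the rule sets them aside. Since post-withdrawal follow-up names weight and HbA1c and no questionnaire, those earlier forms are the only scheduled mood and anxiety data the article describes for leavers.

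Leaving a demanding diet is unlikely to be unrelated to how the person feels on it. If people whose mood or anxiety worsens are more likely to leave, a table of completers shows those who coped. Either diet could then look better tolerated than it was. If leaving also differs between the arms, the side-by-side picture of the intermittent and continuous diets is distorted. The pilot is meant to judge acceptability and inform the case for a definitive trial, so this matters even without a formal test.

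**Working it through.** **Inputs.** N = 79, and the retention target is 48/79 (Outcomes, Primary). For the second scenario, the introduction gives a figure of approximately 25% for "Attrition in intensive CLED studies on people with overweight or obesity". There are four follow-up visits for PHQ-9 and GAD-7 (Table 1).

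**The plan's own figure.** 0.60 × 79 = 47.4, so 48 is the smallest whole number that meets 60%, and 48/79 = 60.8%. The target reproduces.

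**People outside the completer table.**
- At the retention target: 79 − 48 = 31, and 31/79 = 39%.
- At 25% attrition: 0.25 × 79 = 19.75, taken as 20 (25%), leaving 59 completers.

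**Share of follow-up scores left out, per scale.** Assume that completers miss no visit, and that each of L leavers attended k visits before week 52. With C completers, the share is L × k / (4 × C + L × k).

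| Leavers L | Completers C | k = 3 (weeks 8, 12, 28) | k = 1 (week 8 only) |
|---|---|---|---|
| 20 | 59 | 60 / (236 + 60) = 60/296 = 20% | 20 / (236 + 20) = 20/256 = 8% |
| 31 | 48 | 93 / (192 + 93) = 93/285 = 33% | 31 / (192 + 31) = 31/223 = 14% |

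The k = 3 column is an upper bound within each scenario. PHQ-9 and GAD-7 have the same schedule, so the figures apply to each. A person who left before week 8 has no follow-up score, and no reporting rule could recover one.

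**What this could do to a reported proportion.** The article gives no worsening rate, so this is an illustration on assumed rates. Take one visit attended by all 79, say week 8. Suppose 5% of those who later complete have worsened there, and a proportion q of those who later leave. The completer table shows 5.0% whatever q is. The figure for everyone seen at that visit is (C × 0.05 + L × q)/79.

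| q | L = 20, C = 59 | L = 31, C = 48 |
|---|---|---|
| 5% | (2.95 + 1.00)/79 = 5.0% | (2.40 + 1.55)/79 = 5.0% |
| 10% | (2.95 + 2.00)/79 = 6.3% | (2.40 + 3.10)/79 = 7.0% |
| 20% | (2.95 + 4.00)/79 = 8.8% | (2.40 + 6.20)/79 = 10.9% |

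The first row matters as much as the others: if leavers fare no worse than completers, the rule costs precision but causes no bias in this proportion.

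**The case against.** **The outcomes are exploratory.** The trial is a pilot with no significance tests on its primary outcomes and is not powered to compare arms. Completers' PHQ-9 and GAD-7 results will still be shown. This stands, and it limits the weight of the point.

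**The size is mostly assumed.** The 39% comes from a minimum retention target. The 25% comes from other studies of continuous diets and is applied here to both arms. Neither is a forecast. In the illustration with 20 leavers, moving q from 5% to 20% adds 20 × 0.15 = 3 people across two arms. This also stands.

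**Completion is not defined where the rule is stated.** Carrying over the retention measure is an inference. It is the natural one: no other measure is offered, and Retention and Withdrawal also treats people who fail to return for assessments as withdrawn.

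**Other safeguards exist.** Adverse events were recorded, reasons for withdrawal were noted, the steering committee reviewed safety every 3 months, and a psychologist was available to participants in difficulty. These make it less likely that marked distress went unnoticed. None of them reports scores by arm, and nonserious events depended on the participant telling the team.

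**A stronger reading is tempting but not supported.** Table 1 also collects the Binge Eating Scale and AUDIT at weeks 28 and 52, while Exploratory Measures omits them and the analysis text covers only this group: "Questionnaires used as outcome measures are quantitative and will be analyzed using appropriate descriptive statistics as per standard". A reader might infer that worsening binge eating or drinking will go unreported. The article does not say so. EQ-5D-3L is likewise collected and unlisted, which fits an abbreviated list, and the full protocol (V5.0) is not shown. Only the completer rule is stated outright, so the point rests on that alone.

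**Conclusion.** The point holds for PHQ-9 and GAD-7. Followed as written, the plan leaves out mood and anxiety scores already held on anyone who misses the 12-month appointment. That is 31 people at the retention target or about 20 at the cited attrition, with at most 20% to 33% of follow-up scores lost on each scale and 8% to 14% if leavers attended only week 8. These figures rest on taking attendance at 12 months as completion and on completers missing no visits.

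The likely direction, if worsening leads people to leave, is that tolerability looks better than it was. The documents do not show that this happened, or that leaving differed by arm. No primary outcome and no sample-size figure is touched. This is a cheap improvement to consider, not a flaw that undermines the trial.

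**What to change.** In Sample Size and Statistical Analysis, exempt PHQ-9 and GAD-7 from the completer-only rule. At each of weeks 8, 12, 28 and 52, and by arm, summarise all available scores from everyone who attended that visit:

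- change from baseline;
- number scoring 10 or more and number scoring 15 or more, the cut-offs already used under Psychological Support and in the exclusion criteria of Textbox 1;
- the denominator at that visit;
- baseline scores of later leavers and of completers alongside.

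Keep the summary visit-specific. A count of those who ever reached a cut-off would give completers four chances and an early leaver as few as one, so arms with different attrition would still not be comparable. Because entry was capped on these same scores, some later crossings of the cut-off of 15 will reflect regression to the mean; the table should be read with that in mind.

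Label the table as added after data collection (completed February 2020) and after analysis began (June 2020).

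The cost is one descriptive table from data already held. The downsides are denominators that change from visit to visit and small counts in each arm.
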